The prevalence of pneumonia complicating stroke in acute phase is ~ 20 to 60% [12, 13]. Although it is not the most frequent medical complications following stroke, it may be the most difficult to manage and has a very poor prognosis, leading to a threefold risk of death [14, 15]. Although it occurs most often within 1 week after the onset of stroke, yet it can still develop in 6 to 30 months after stroke [13]. Prophylactic use of antibiotics to reduce the incidence rate of stroke-associated pneumonia has proved to be of little use in a multi-center randomized controlled trial [16]. Therefore, new preventive approaches for stroke-associated pneumonia aiming at reducing respiratory pathogens in the oral cavity are urgently needed.

Oral health promotion is a range of activities which enable individuals and communities to increase control over the determinants of oral health and thereby improve their oral health. Since dental plaque is associated with many oral diseases, the major composition of oral health promotion interventions aims at removing dental plaque. Dental plaque removal measures include mechanical and chemical measures. Powered tooth brushing has been proved to be more effective than manual tooth brushing in reducing plaque and gingivitis [17]. Chlorhexidine is the gold standard among those chemical plaque control measures, and its antiplaque effectiveness has been well established [18]; however, its effectiveness against oral opportunistic pathogens in the clinical setting is unclear [9].

Moreover, oral health-related quality of life (OHRQoL) reflecting an interaction between oral health conditions and their contextual cultural factors is now recognized as an important parameter in outcome assessment of oral health in epidemiological studies and clinical trials. OHRQoL consists of functional (biting, chewing, swallowing, and speaking) and psychosocial wellbeing (concerns about certain oral conditions and satisfaction with respect to oral care and self-image of appearance) [19]. Therefore, it is also critical to assess the effectiveness of oral health promotion intervention in improving subjective oral health among patients with stroke.

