The following selection criteria are applied: (1) having onset of stroke within 3 days and free of any post-stroke complication; (2) having moderate to severe functional disability—Barthel Index (BI) scores of < 70; (3) being conscious and respiring voluntarily without ventilator; (4) not having any lung disease and lower respiratory infection; (5) not having indwelling naso-gastric feeding tubes; (6) having dysphagia as shown by Gugging Swallowing Screen (GUSS) test; (7) having normal cognitive ability or mild impairment—Mini-Mental State Examination (MMSE) > 18; (7) having the ability to follow instructions (as an assessment of compliance of oral health intervention); (8) not having systemic administration of antibiotics; and (9) not being edentulous. Patients who meet the above selection criteria will be provided with detailed information regarding potential benefits and adverse effects of the interventions, the procedures of this trial, and the anticipated outcomes. They will be asked by a researcher in our team to sign on a written informed consent before enrolling in this study (written informed consent, additional file 3).

According previous studies [12, 13], pneumonia complicating stroke usually occurs within 1 week after stroke. We set the prevalence of pneumonia within 1 week after onset of stroke as the primary outcome of this study since we would like to explore whether oral health promotion interventions could possibly reduce the prevalence of pneumonia after stroke. According to previous epidemiological studies, the prevalence of pneumonia complicating stroke is 20 to 60% [12, 13]. Thus, we hypothesize that in the comparison group, the prevalence of pneumonia complicating stroke within 1 week is 40%, while the prevalence could be decreased to the lower limit of 20% in the interventional group. We set the statistical power at 80% and the statistical significance level at 0.05. Anticipating a 10% dropout rate over the first week of this clinical trial, the initial sample size for each group is proposed as 83 patients per group (166 subjects in total, Gpower 3.0.10 statistical software).

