### Outcomes

The primary outcome is the prevalence of pneumonia complicating stroke within 1 week after baseline. The secondary outcomes include the following: (1) the prevalence of pneumonia complicating stroke within 1, 3, and 6 months after baseline; (2) metagenomic outcomes in terms of composition and relative abundance of oral microbiome in oral rinse samples in 3, 5, and 7 days, and 1, 3, and 6 months after baseline; (3) oral hygiene status and gingival bleeding in 1, 3, and 6 months after baseline; and (4) generic health-/oral health-related quality of life in 1, 3, and 6 months after baseline. The time point for assessing each outcome is illustrated in Fig. 1.

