#### Data management

The principal investigator will oversee the data collection, entry, analyses, and reporting. Two researchers in our team will conduct data proofreading after the completion of data entry. The data will be securely stored in SPSS files in a computer with a password. The statistics software packages SPSS 25 for Windows (SPSS Inc., Chicago, USA) and QIIME 2 will be used to analyze the data. Per-protocol (PP) will be employed for both primary and secondary outcomes in bivariate analyses. Within- and between-group comparisons will be conducted over the clinical trial period. When the outcome variables are continuous and follow a normal distribution, a paired *t* test for related samples will be performed to determine the significant differences over time within a group. The Student *t* test for independent samples will be performed to compare the mean of the outcomes between the groups at baseline and follow-up reviews. When the outcome variables are continuous but do not follow a normal distribution, the Wilcoxon signed-rank test will be performed to determine the significant differences over time within a group. The Mann-Whitney *U* test will be employed to compare the differences in the rank of outcomes between the groups at baseline and follow-up reviews. When the outcome variables are categorical, the McNemar test will be performed to identify the changes in prevalence over time within a group. The chi-square test will be employed to compare the variations in prevalence between the groups at baseline and follow-up reviews. Regression analyses will be employed to address the effect of confounding factors for outcomes. When conducting the regression analysis, the method of Last Observation Carried Forward (LOCF) will be employed to deal with missing outcomes at follow-up reviews. Linear regression will be adopted when the dependent variables are continuous, and the residuals of the regression followed a normal distribution. Negative binomial regression will be adopted when the distribution of the continuous dependent variables is over-dispersed. Logistic regression will be adopted when the dependent variables are binary.

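### In the adjusted regressions, last observation carried forward codes every patient lost without a recorded episode as pneumonia-free

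*Protocol article*

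**What the plan says.** All statements are from the protocol article.

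- **Missing outcomes (Data management):** for the regression analyses, "the method of Last Observation Carried Forward (LOCF) will be employed to deal with missing outcomes at follow-up reviews". No outcome and no cause of missingness is exempted.
- **Model for pneumonia (same section):** "Logistic regression will be adopted when the dependent variables are binary".
- **Unadjusted tests (same section):** "Per-protocol (PP) will be employed for both primary and secondary outcomes in bivariate analyses". No LOCF is stated for these.
- **Outcome (Outcomes):** "The primary outcome is the prevalence of pneumonia complicating stroke within 1 week after baseline". Pneumonia within 1, 3 and 6 months is secondary.
- **Status at entry (Participants):** the criteria include "having onset of stroke within 3 days and free of any post-stroke complication" and "not having any lung disease and lower respiratory infection".
- **Ascertainment (Assessment of pneumonia complicating stroke):** in-hospital diagnosis in the first week is called feasible. Diagnosis after discharge is called challenging and relies on medical history and notes at follow-up visits.
- **Prognosis (Background):** pneumonia is described as "leading to a threefold risk of death".

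**The concern.** LOCF needs an earlier value to carry. For pneumonia the first value is absent for everyone, by eligibility. In the logistic regressions LOCF is therefore the same as imputing no event for each patient who is lost without a recorded episode.

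That would matter little if missingness were unrelated to pneumonia, but the protocol gives reason to doubt this. After discharge, pneumonia is found at follow-up visits. A patient who develops it at home and then dies, or is too ill to attend, has no such visit unless the information arrives another way. LOCF would count that patient as a non-case.

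The continuous outcomes have a related problem. Plaque, gingival bleeding and quality of life are measured at baseline and at 1, 3 and 6 months. A patient lost before month 1 has only the baseline value, taken within days of stroke onset, and LOCF carries it to 6 months. The model then treats the copied value as observed, so its uncertainty is not reflected in the standard errors.

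At stake are recorded risks that are too low in both arms and, if loss differs between arms, a biased adjusted treatment effect.

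**Working it through.** **Inputs from the protocol (Participants):** control risk 40%, intervention risk 20%, significance level 0.05, power 80%, 10% dropout in the first week, 83 per group. **Not given, so assumed below:** loss by arm, the pneumonia risk of lost patients relative to their arm (*r*), and the timing of loss within the week.

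**1. The plan's own figure.** A one-sided, continuity-corrected two-proportion calculation gives 74 per group, and 74/0.9 = 82.2, rounded up to 83. A two-sided calculation without correction gives 82 before any dropout. The sidedness is not stated. That is a separate matter, and nothing below depends on it except that *n* = 83.

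**2. Formulas.** If a share *d* of an arm with true risk *p* is lost before onset, the risk recorded under LOCF is *q* = *p* − *d·r·p*. With *r* = 1 this is *p*(1 − *d*).

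The two-sided rejection probability uses D = *q*₁ − *q*₂, *q̄* = (*q*₁ + *q*₂)/2, *s*₀ = √[2*q̄*(1 − *q̄*)/*n*] and *s*₁ = √[(*q*₁(1 − *q*₁) + *q*₂(1 − *q*₂))/*n*]. It equals 1 − Φ[(1.96*s*₀ − D)/*s*₁] + Φ[(−1.96*s*₀ − D)/*s*₁].

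**3. Equal loss of 10%, *r* = 1.** Control: 0.40 × 0.90 = 0.36. Intervention: 0.20 × 0.90 = 0.18.

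| Data | Risks | n per arm | Difference | Power |
|---|---|---|---|---|
| Complete follow-up | 40% vs 20% | 83 | 20 points | 80.9% |
| Complete cases (83 × 0.9 = 74.7, taken as 75) | 40% vs 20% | 75 | 20 points | 76.7% |
| LOCF | 36% vs 18% | 83 | 18 points | 74.7% |

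For the LOCF row, *s*₀ = 0.0689 and *s*₁ = 0.0675, so (0.18 − 1.96 × 0.0689)/0.0675 = 0.67 and Φ = 0.747.

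The risk ratio stays at 0.50. True odds ratio: (0.20/0.80)/(0.40/0.60) = 0.375. Under LOCF: (0.18/0.82)/(0.36/0.64) = 0.390.

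**4. Unequal loss, no true effect (40% in both arms).** The illustrative assumption is 5% loss in one arm and 15% in the other, all before onset.

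- *r* = 1: 0.40 × 0.95 = 0.38 and 0.40 × 0.85 = 0.34. The difference is 4 points and the rejection probability 8.3%.
- *r* = 1.5: 0.40 − 0.05 × 0.60 = 0.37 and 0.40 − 0.15 × 0.60 = 0.31. The difference is 6 points and the rejection probability 12.9%.

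Swapping the losses between arms reverses the sign and leaves the size unchanged. The arm that loses more patients looks better.

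**5. Limits of these figures.** The power and error rates are for an unadjusted two-proportion comparison and serve as a guide to the adjusted logistic regression, the analysis to which LOCF is assigned. They also assume that every lost patient leaves before onset. If half of the lost patients' risk had already been observed and recorded, the effective *d* in step 3 would be 0.05 and the recorded risks 38% vs 19%.

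**The case against.** **The rule covers only part of the analysis.** This stands. LOCF is stated for the regressions alone. A reader might infer that the unadjusted chi-square comparison of pneumonia is also built on LOCF, but the protocol assigns that test to the per-protocol set and states no LOCF for it. The point remains for the regressions, which carry the confounder adjustment.

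**Counting a patient who dies without pneumonia as a non-case is correct.** This also stands. A reader might infer from the threefold risk of death that LOCF misclassifies deaths in general. It does not. A recorded episode is carried forward as a case, and a death with pneumonia confirmed absent is a legitimate non-event. The error concerns patients whose status was not ascertained, mainly after discharge.

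**The effect on the primary outcome is small.** Largely true under equal loss: about 2 points of power below complete cases, an unchanged risk ratio and a slightly shifted odds ratio. Most patients are in hospital that week, so the 10% scenario is an upper bound for losses at average risk.

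**Unequal loss is speculative.** Its size and direction are. The intervention arm has the heavier routine, but the comparison arm receives the products only after the trial ends, so either arm could lose more. A reader might infer that LOCF flatters the intervention, but the documents do not establish that.

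**The 6-month bias could be thought much larger.** A reader might apply *p*(1 − *d*) with the 40% risk to all loss by 6 months. That would require every loss to precede any pneumonia, whereas the Background places most cases in the first week, when status is usually known. Later loss can hide only late-onset cases. If one arm loses a further 20% after week 1 and late incidence is 5 to 10 points (both assumed), the spurious difference is 0.20 × 5 = 1 point to 0.20 × 10 = 2 points.

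**Conclusion.** The point holds for the adjusted regressions. It is a stated rule with a predictable bias, so it is not a detail left to an analysis plan. For an outcome that is absent in everyone at entry, LOCF imputes no event for each lost patient without a recorded episode, including those with unrecorded pneumonia after discharge.

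Under equal 10% loss before onset, the cost is a difference that shrinks from 20 to 18 points and power of about 75%, lower than if the missing patients were simply omitted. Under an assumed 5% vs 15% loss with no true effect, a 4-point difference arises and the false-positive rate is about 8%, or about 13% if lost patients carry 1.5 times the average risk. Losses by arm, *r* and the timing of loss are assumptions. The protocol gives only 10% overall for the first week, and no figure for later loss or death.

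For plaque, bleeding and quality of life, the fault is an acute-phase value carried to 6 months and analysed as if observed. Its size cannot be computed from the protocol.

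**What to change.** Delete LOCF from the regression paragraph in Data management and replace it as follows.

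- **Pneumonia within 1 week:** include all randomised patients. Multiply impute unascertained status within arm from baseline variables already collected, such as age, smoking, cognition, comorbidities and the screening scores for swallowing and function. A patient who died with pneumonia confirmed absent stays a non-event and is not imputed.
- **Pneumonia within 1, 3 and 6 months:** analyse event dates, with censoring at last contact and death as a competing event.
- **Continuous outcomes:** use a mixed model for repeated measures on all available visits, with no imputed values carried forward.

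Other principled methods would also serve; what matters is that an unknown status is not set to no event by default. The replacements have assumptions of their own: the imputation needs the baseline variables to explain the missingness, and the time-to-event analysis needs uninformative censoring.

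The cost is a change of wording, modest extra programming, and the recording of dates of pneumonia, death and last contact. Sample size, visits and interventions do not change.

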#### Clinical oral health assessment

Oral hygiene status will be assessed by Silness and Löe Plaque Index (PI) [23]. The PI will be assessed at six sites per tooth and charted on all permanent teeth. The criteria for the Silness and Löe PI are as follows: 0 = no plaque detected with probe, 1 = plaque not visible by unaided eye but detectable with probe, 2 = moderate amount of plaque, and 3 = abundance of plaque. The percentage of tooth sites with moderate to abundant plaque (PI score, 2 or 3) will be calculated for each subject. Gingival bleeding will be assessed by the Gingival Bleeding Index (GBI) [24]. The GBI will be charted on all permanent teeth and assessed at six sites per tooth. The criteria for GBI are 0 = no bleeding after probing and 1 = presence of bleeding within 10 s after probing. The percentage of bleeding sites (GBI score, 1) will be calculated for each subject. At each study visit, ~ 10% of the subjects will be randomly selected for the reevaluation of the PI and GBI and the intra-rater reliabilities will be evaluated. Other clinical oral health outcomes including dental caries experience (DMFT), oral mucosa conditions, and dental prosthesis status will be recorded according to WHO Basic Oral Health Survey Guidelines [25].

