#### Subjective health assessments

The subjective health assessment includes generic health-related quality of life (HRQoL) and oral health-related quality of life (OHRQoL) assessments. Patients will be interviewed with Chinese versions of the Short Form Health Survey 12 (SF-12) [26], the Oral Health Impact Profile 14 (OHIP-14) [27], and the Geriatric Oral Health Assessment Index (GOHAI) [28]. The SF-12 consists of 12 items, and each of them has its own physical component summary (PCS) and mental component summary (MCS) regression coefficients [29]. The response to each item will be multiplied by its PCS regression coefficient and added together with the PCS constant to provide Physical Health summary scores (SF-12 PCS). Mental Health summary scores (SF-12 MCS) will be calculated likewise. For OHIP, responses to the frequency of an event occurring as described by each item are coded on a 5-point Likert scale: 0 = never, 1 = hardly ever, 2 = occasionally, 3 = fairly often, and 4 = very often/all of the time. Summary OHIP-14 score and domain scores will be derived by summating responses to each item (i.e., scores 2, 3, and 4) [30]. For GOHAI, responses to the frequency of an event occurring as described by each item are coded using a 5-point Likert scale: 1 = always, 2 = often, 3 = sometimes, 4 = seldom, and 5 = never. Summary GOHAI scores will be derived by summating responses to items after reversing the coding of the three positively worded items (swallowing, appearance, and discomfort when eating) [31].

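### Negative binomial regression is assigned to over-dispersed continuous outcomes, but plaque, bleeding, SF-12 and GOHAI are bounded percentages or scores, not counts; the trigger is not meaningful for them and overlaps with the linear-regression rule

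*Protocol article*

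**What the plan says.** The Data management section gives three rules for the regressions that adjust for confounders:

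- Continuous, normal residuals: "Linear regression will be adopted when the dependent variables are continuous, and the residuals of the regression followed a normal distribution".
- Continuous, over-dispersed: "Negative binomial regression will be adopted when the distribution of the continuous dependent variables is over-dispersed".
- Binary: "Logistic regression will be adopted when the dependent variables are binary".

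It does not define over-dispersion, rank the first two rules, or give a dispersion or standard-error setting. The software for these analyses is SPSS 25.

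The numeric outcomes are defined elsewhere. Under Clinical oral health assessment, for plaque: "The percentage of tooth sites with moderate to abundant plaque (PI score, 2 or 3) will be calculated for each subject"; for bleeding: "The percentage of bleeding sites (GBI score, 1) will be calculated for each subject". Under Subjective health assessments, the SF-12 physical summary is a weighted sum with an added constant ("The response to each item will be multiplied by its PCS regression coefficient and added together with the PCS constant"), and the mental summary is built likewise. GOHAI is a sum of items coded 1 to 5: "Summary GOHAI scores will be derived by summating responses to items after reversing the coding of the three positively worded items". OHIP-14 is a sum of items coded 0 to 4. DMFT is recorded among the other clinical findings.

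**The concern.** Negative binomial regression describes non-negative counts without an upper limit, and over-dispersion is a property of counts: more variance than a Poisson variable with the same mean. A percentage of sites has a ceiling. An SF-12 summary is not a count at all, and a GOHAI total cannot reach zero. Read literally, the rule sends some or all of these outcomes to a model that does not fit their scale, on a criterion with no interpretation for them.

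The rule also overlaps with its neighbour. An outcome can have normal residuals and a variance above its mean, so two models are prescribed. One with non-normal residuals and a variance below its mean has no model. In either case the choice falls to the analyst after the data are seen. At stake are the adjusted analyses of oral hygiene, gingival bleeding and quality of life, which serve the third and fourth stated aims.

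**Working it through.** The article gives no mean, SD or power for these outcomes, so there is no plan figure to reproduce. All means and SDs below are assumptions. The number analysed comes from the sample-size paragraph: 83 per group less 10% dropout, 83 × 0.9 = 74.7, taken as 75 per arm.

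**1. Is the trigger meaningful?** Take over-dispersion as variance/mean above 1.

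- Plaque in percent, mean 60, SD 20: 20²/60 = 6.67. The rule applies at this mean whenever the SD exceeds √60 = 7.7 points.
- The same data as a proportion: 0.20²/0.60 = 0.067. A variable confined to 0–1 with mean m has variance at most m(1 − m), which is below m, so it can never trigger the rule.
- The ratio changes by a factor of 100 with the unit, so it does not measure lack of fit.

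**2. Do the two rules overlap?** An SF-12-like score with mean 40, SD 10 and normal residuals has variance/mean 10²/40 = 2.5, so both rules apply. A GOHAI-like score with mean 48 and SD 7 has 7²/48 = 1.02, right at the threshold (√48 = 6.9).

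**3. What does it cost?** Simulation, 400 runs per setting. Percentages were drawn from beta distributions, with the difference set for about 80% power under linear regression. Power in percent (NB = negative binomial):

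| Assumed mean (SD) | Linear | NB, dispersion estimated | NB, dispersion 1, robust errors | NB, dispersion 1, model-based errors |
|---|---|---|---|---|
| 20 (15) | 76.5 | 70.8 | 74.2 | 68.2 |
| 30 (15) | 82.8 | 78.5 | 82.5 | 27.8 |
| 30 (20) | 80.2 | 73.2 | 80.0 | 65.0 |
| 50 (20) | 77.2 | 73.5 | 77.5 | 3.8 |
| 50 (25) | 82.0 | 71.5 | 82.0 | 25.5 |
| 60 (25) | 76.0 | 68.8 | 76.8 | 5.8 |
| 70 (20) | 77.2 | 70.5 | 78.5 | 0.0 |
| GOHAI-like 48 (7) | 81 | 69 | not run | 0 |
| SF-12-like 40 (10) | 78 | 78 | not run | 0 |
| OHIP-like, skewed, 10 (9) | 95 | 96 | not run | 91 |

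Simulation error is about √(0.8 × 0.2/400) = 2 points.

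- Dispersion estimated: the loss on percentages runs from 77.2 − 73.5 = 3.7 to 82.0 − 71.5 = 10.5 points. On scores it runs from none to 81 − 69 = 12. The 12 is an upper figure: with variance/mean near 1 many of these fits fail, and failures were counted as non-significant.
- Robust errors: the largest loss is 76.5 − 74.2 = 2.3 points, about the size of simulation error.
- Type I error on percentages: 1.5–3.5% with dispersion estimated, 3.2–5.8% with robust errors, 0–0.2% with dispersion 1 and model-based errors, against 3.0–5.0% for linear regression.

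**4. Why fixing the dispersion at 1 is harmful.** It assumes variance = mean + mean². Check by hand for mean 50, SD 20, with the other arm lower by 20 × (1.960 + 0.842) × √(2/75) = 9.15, that is 40.85:

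- Log ratio: ln(50/40.85) = 0.202.
- Model-based SE: √[(1/50 + 1 + 1/40.85 + 1)/75] = 0.165.
- True SE: √[((20/50)² + (20/40.85)²)/75] = 0.073.
- Power: Φ[(0.202 − 1.96 × 0.165)/0.073] = Φ(−1.66) ≈ 5%, in line with the simulated 3.8%.

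**The case against.** The strongest reply is that this is loose wording with little consequence. Continuous may simply mean numeric, and the rule has proper uses: DMFT is a count, and OHIP-14 is a non-negative integer sum for which the model lost little or nothing. An analyst would reach for it mainly with right-skewed data, where losses are smaller even with dispersion fixed at 1 (76.5 against 68.2 at mean 20, SD 15). The near-zero power for GOHAI and SF-12 comes from data simulated as approximately normal, which the preceding sentence sends to linear regression. Dispersion and error settings are also details that an article leaves to the fuller plan. All of this stands, and it limits the size of the point. It does not rescue the rule, which is stated for continuous outcomes at large and gives no precedence when both conditions hold.

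Three stronger readings are tempting and not supported:

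- That these analyses will lose most of their power. This needs the dispersion fixed at 1 together with model-based errors, and the article states neither.
- That the choice between percent and proportion is left open, so that the unit decides the model. The article fixes the unit as a percentage; the factor of 100 shows only that the criterion is unsound.
- That inference would be invalid through false positives. The simulated type I error is conservative or nominal.

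Ignoring the number of sites examined is not a fault peculiar to this rule either; a t test or linear regression on the percentage does the same.

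**Conclusion.** The point holds in a limited form. The article assigns a count model to outcomes that it defines as bounded percentages and scores, on a trigger that has no sound meaning for them and can hold together with the linear-regression condition. The rule could select a mis-specified model; it need not do so.

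The expected cost is a power loss of about 0 to 12 points with estimated dispersion and about 0 to 2 points with robust errors. A near-total loss is confined to one software configuration that the article does not mention. These figures rest on assumed means, SDs and distribution shapes and on 75 analysed per arm, which uses the first-week dropout although these outcomes are measured at 1, 3 and 6 months.

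The reach is narrow: only the confounder-adjusted analyses of secondary outcomes. The primary pneumonia outcome is binary and goes to logistic regression, and the unadjusted comparisons of continuous outcomes use t or rank tests.

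**What to change.** Replace the sentence on negative binomial regression with a model fixed in advance for each outcome:

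- Plaque and bleeding percentages: fractional-logit (quasi-binomial) regression, or linear regression, with robust standard errors. Either is acceptable; name one.
- SF-12 summaries and GOHAI: linear regression with robust standard errors.
- DMFT, and OHIP-14 if skewed: negative binomial regression with the dispersion estimated from the data.

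Remove the switch based on residual normality or over-dispersion for the percentages, SF-12 and GOHAI. This changes a sentence or two of the analysis text and can be done before analysis. It alters no data collection and no sample size, and costs the trial nothing.
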